## Trial design {8}

The study is a randomised 2 × 2 factorial trial, using four conditions: IIMT, IIMT with an additional component of music listening (ML), IIMT with an additional component of vibroacoustic treatment (VAT), and IIMT with the additional elements of both ML and VAT. A superiority design is adopted with the aim of testing whether the intervention, in different conditions, demonstrates statistically and clinically superior outcomes compared with the comparator.

All sessions regardless of the condition will begin with a preparing exercise called Resonance Frequency Breathing (RFB) [24]. There will be a waiting-list control group to whom the plain IIMT will be offered after six weeks of baseline measurements, allowing a within-subject comparison between baseline and treatment conditions. Each group is offered a therapy process consisting of 12 sessions, conducted twice a week for 60 min each.

Outcomes will be measured before and after the start of the therapy and at two follow up points, 6 months and 12 months after the start of the therapy. For Condition A there will be additional baseline 2 measurements before the start of the therapy (see Fig. 1).

**Fig. 1 Fig1:**
[figure not shown]
The flow-chart of the iMTDep RCT

## Methods: Participants, interventions and outcomes

### Study setting {9}

The study will be conducted in an academic setting at the JYU Music therapy clinic for research and training at the University of Jyväskylä, Finland. All the data will be collected in Finland.

### Eligibility criteria {10}

Participants are included if they score 15 or higher on MADRS [25] and/or 7 or higher on HADS-A [26] and/or 19 or higher on KEDS [11]. Exclusion criteria are psychosis, a recognized personality disorder, acute substance abuse (measured with AUDIT [27]), difficulty in engaging in the study and too severe depression (e.g. self-destructive behaviour or chronic depression) for participation in therapy. In addition, the participants are excluded if they are pregnant or have a pacemaker, as those conditions are contraindications for participating in the VAT.

The Research Centre has former experience of conducting RCT studies [23, 28]. The facilities and equipment have been technically renewed in 2021–2023 to meet the current research needs of The Centre of Excellence in Music, Mind, Body and Brain (MMBB). All assessments will be performed by qualified health care personnel with experience of assessment, evaluation and psychometric testing. All interventions will be performed by qualified music therapists that have undergone uniform protocol training for working as interventionists in this study setting. Adherence to the intervention protocol will be monitored in clinical supervision.

### Who will take informed consent? {26a}

The assessors will collect the informed consent from participants, after they are screened and assessed for eligibility. If they meet the inclusion criteria (sufficient score in the screening with MADRS, HADS-A and/or KEDS) and do not meet any of the exclusion criteria, they will be asked to give their consent to participate in the study. After giving their consent, the other baseline measurements are conducted in the same session.

### Additional consent provisions for collection and use of participant data and biological specimens {26b}

Not applicable; no additional consent is needed, and no biological samples are collected.

## Interventions

### Explanation for the choice of comparators {6b}

The Condition A serves as a waiting-list control group, and they receive their intervention after a 6-week waiting period. This group will serve as the comparator for the primary intervention. Throughout the study all participants in all groups will receive regular healthcare (treatment as usual).

### Intervention description {11a}

The intervention consists of 12 therapy sessions (60 min twice a week) in an individual setting. The intervention is based on a treatment model developed at our unit and previously utilised in two RCTs [23, 28]. This intervention is called Integrative Improvisational Music Therapy (IIMT). In this trial, there are four different conditions, which are modifications of IIMT (except for Condition A, which consists solely of IIMT). Despite these modifications, IIMT remains the primary intervention. The modifications in Conditions B, C, and D occur at the beginning of the sessions and are as follows: ML + IIMT (Condition B), VAT + IIMT (Condition C), and VAT with ML + IIMT (Condition D). Detailed descriptions of all conditions are provided in the following section.

#### IIMT only

Condition A (IIMT only) begins with a 7-min RFB exercise [24]. Following this, the session proceeds with IIMT activities, which include clinical improvisation and discussion. The total session duration is 60 min, with approximately 40 min dedicated to IIMT activities. In the IIMT model, the length and number of improvisations, as well as the amount of discussion, are not predefined but are determined intuitively by the therapist and client. The musical instruments used in IIMT are identical for both participants: a djembe drum and a digital keyboard with piano sounds for both the therapist and the client, ensuring equal instruments for both improvisers.

#### IIMT with music listening

Condition B begins with a 7-min RFB exercise and includes an additional component of music listening prior to IIMT. The recommended duration for this component is 15 min but may vary slightly depending on the situation. Music selection can be made by the client or the therapist, depending on the current needs of the moment. A typical starting point is to listen to music, which is somehow meaningful or currently important to the client.

#### IIMT with vibroacoustic treatment

Condition C begins with a 7-min RFB exercise and includes an additional component of vibroacoustic treatment used prior to IIMT. The recommended duration for this component is 15 min, though it may vary slightly depending on the dynamics of the moment.

#### IIMT with vibroacoustic treatment combined with music listening

Condition D begins with a 7-min RFB exercise and combines the additional elements of vibroacoustic treatment and music listening prior to IIMT. The recommended duration for this component is 15 min, though it may vary slightly depending on the dynamics of the moment.

### Integrative improvisational music therapy (IIMT)

IIMT is a music therapy model [3], which consists of clinical improvisation usually with two similar pianos and djembe drums in a client-therapist dyad, and reflection of the experience in verbal discussion. It originally roots back to psychoanalytical ideas about the meanings of music in improvisational music therapy which can be used in a psychodynamic context as well as in psychodynamic psychotherapy. Improvisational music therapy, such as IIMT, is suitable for all client groups, and does not require specific musical training from the client. The model can be successfully applied even to clients with limited ability for verbal expression. As a form of non-verbal expression and interaction, clinical improvisations can lead to the emergence of the client’s abstract and unshaped mental contents from the subconscious to the conscious level. These experiences are often accompanied by emotional aspects. Adults with typically developed cognitive skills and capacity of abstract thinking can connect symbolic and experience-based mental contents to their musical expression in the context of clinical improvisation [29]. The effectiveness of IIMT has been proven to be significant compared to standard care with depressed patients, and to be enhanced by adding a breathing exercise called Resonance Frequency Breathing (RFB) [28, 30]. In this study, RFB is integrated in the beginning of every therapy session to prepare the client for improvisation and enhance the effect of IIMT. The individual optimal breathing pace is defined before the start of the therapy process by conducting an individual breathing test for each participant. The test is based on heart rate variability (HRV) measurement [24].

### Music listening

Receptive techniques [31] are one of the main intervention families in music therapy consisting of various models and methods based on music listening. In our study, we will utilise both sedative and stimulating musical stimuli according to a client’s current needs. There are a few factors, which determine sedative and stimulating musical experience. According to the most universal principles we will put attention to certain basic determinants such as high frequencies (tension related), and low frequencies (relaxation related), strong rhythm (energy and activity) versus rhythmically neutral music (calmness), and loud music (arousal and awareness) versus soft music (pacifying, calming, relaxing) [32]. According to research evidence [32] most effective music to use is the music familiar and preferred by the client. However, sometimes also the therapist must make a choice – for instance, when a client asks for it. In this study, both music selection types are allowed. Both instrumental and vocal music are possible. In music listening intervention, therapeutic relationship (dialogue) between client and music therapist is involved, which makes the intervention music therapeutic according to the definition by Bruscia [33]. In addition to goals such as relaxation and stimulation, music listening is widely used in music therapy for evoking images and emotional memories, which often are connected to therapeutically meaningful themes [31, 34].

### Vibroacoustic treatment with or without music listening

Vibroacoustic treatment can be considered as a form of receptive music therapy, which can be applied with or without music listening. It uses low frequency (20–120 Hz) sinusoidal sound vibration, delivered through a device with loudspeakers or transducers. Vibroacoustic treatment can be directed locally or as a full-body stimulation. The main concept of vibroacoustic treatment is sympathetic resonance, which occurs in the body when the sound vibration affects the certain resonant body parts [35]. The vibrating effect in a body may support either relaxation or activation, depending on the speed of pulsation (amplitude change over time). Also, listening to music can be calming down or activating, for instance, evoking imagery or triggering some memories. In vibroacoustic treatment both psychological and physiological processes can be observed in the same situation. This allows reflective therapeutic discussion on the levels of thoughts and memories (cognitive), images (symbolic), feelings (emotional), and bodily sensations (physiological). An integrative view to a client’s experiences offers a possibility to work on different thematic content, and to further process these in active music therapy, in this case, by using IIMT [32, 35, 36]. In this study, vibroacoustic treatment is offered for 15 min as 40 Hz sinusoidal sound vibration with 6,8 s curve of amplitude change. The only adjustable parameter is the overall volume level of the stimulation, which will be individually set to a comfortable level.

#### Criteria for discontinuing or modifying allocated interventions {11b}

The participants have the right to withdraw from the study at any point. The need to discontinue the intervention may arise, for example, due to the participant’s strongly weakened condition, physical limitations or changes in life situation. The possibility of modifying or discontinuing the intervention will be discussed between the assessor, supervisor, therapist and participant, considering participants’ wishes and any safety-related concerns. Therapists participate in group supervision, where possible modifications of the intervention or discontinuation of the intervention can be further discussed. The consulting psychiatrist may be contacted if needed.

#### Strategies to improve adherence to interventions {11c}

All the clinically qualified music therapists are obligated to complete an additional intervention training consisting of theory, practical demonstrations, workshops, collaborative reflection, technical guidance, and independent rehearsals in dyads or triads. The training period lasts approximately 5 months and is conducted on weekly basis, four hours per time. After the training the therapists participate in weekly group supervision sessions (for four hours each) throughout their clinical work. The adherence to treatment protocol is assessed by monitoring the video recordings of the therapy sessions frequently as part of the supervision. The therapists fill out a session questionnaire after each therapy session for self-reflection and reporting of their own observations. Individual clinical supervision may be arranged in special occasions as needed for ensuring the adherence to protocol and treatment fidelity.

#### Relevant concomitant care permitted or prohibited during the trial {11d}

During the trial, the participants are permitted to receive all standard treatment, and their other ongoing therapies are not prohibited. Possible changes in care, rehabilitation and/or complementary treatments will be recorded by the assessors during the appointments.

#### Provisions for post-trial care {30}

This study itself is not responsible for offering post-trial care for the participants, but when needed, the participant is informed about the local psychiatric and health care services they can contact to receive additional care. The consulting psychiatrist can also be contacted to evaluate a participant’s situation.

#### Outcomes {12}

All the primary and secondary outcome measures will be assessed at baseline, post and follow-up testing timepoints (see Table 1 below).

**Table 1 Tab1:**
[figure not shown]
Outcomes according to study period

### Primary outcome

The primary outcome measure of this study will be Clinical Outcomes in Routine Evaluation – Outcome Measure (CORE-OM) [37]. It is a 34-item self-report measure that will be used to address the distress and life/social functioning of the participants. The Finnish version of CORE-OM has been found to be reliable and valid assessment tool for psychological distress in both clinical and non-clinical settings [38].

### Secondary outcomes

There will also be several secondary outcome measures. The Montgomery Åsberg Depression Rating Scale (MADRS) (also used for screening for eligibility) [25] will be used to assess the severity of depressive symptoms. A 10-item questionnaire is based on an interview conducted by a clinician. The MADRS has high joint-reliability, it has been shown to be sensitive to change, and it has also been demonstrated to have predictive validity for major depressive disorder [39]. The anxiety subscale (HADS-A) (also used for screening for eligibility) of the Hospital Anxiety Depression Scale (HADS) [26] will be used to assess the level of anxiety. The HADS is a well-established self-report questionnaire that has been widely used for assessing anxiety and depression in a non-psychiatric adult population. The HADS-A consists of seven items. The Finnish translation has been shown to be reliable and internally consistent short and user-friendly instrument [40].

Work-related stress and exhaustion will be assessed with the Karolinska Exhaustion Disorder Scale (KEDS) (also used for screening for eligibility) [11] and the Burnout Assessment Tool (BAT) [41]. The KEDS is a nine-item summated self-rating scale that has been developed to assess symptoms of stress-included exhaustion disorder. The scale has shown to be unidimensional and internally consistent [11]. The BAT is a self-report questionnaire developed to measure burnout [41]. The original BAT consists of 23 items. The shortened 12-item version BAT-12 has shown to have similar psychometric properties than the full version and is well suited for research purposes [42]. There are yet two versions available of BAT-12, a work-related and a general version, that will both be utilised in this study because the work-related version cannot be filled by those currently not working.

RAND-36 will be used to assess the health-related quality of life. The focus of the 36-item survey is on eight quality of life -related domains that are physical functioning, bodily pain, role limitations due to physical health problems, role limitations due to personal or emotional problems, emotional well-being, social functioning, vitality, and general health perceptions. The Finnish version of the RAND-36 has also found to be reliable, valid and adequate in measuring the health-related quality of life [43]. Toronto Alexithymia Scale (TAS-20) will be used to assess the possible alexithymia since it is a reliable and valid measure of alexithymia [44]. The Finnish version of TAS-20 has been shown to operate satisfactorily [45].

### Other assessments

The measures conducted during the recruitment of the participants will also be the ones that determine participants’ eligibility for the study. In addition to the outcome measures demographics such as gender, age and socio-economic background will be inquired at the baseline testing. The health care professional responsible for testing will collect the health background information, such as medication and ongoing or planned treatment and therapies. Possible changes in treatment and care during the research process will also be recorded in testing appointments. The 50-item version of Big Five Inventory will be used to assess the personality dimensions of the participants. The Big Five or the five-factor model is a working consensus regarding the descriptive structure of personality traits [46]. Acute substance abuse will be screened by the Alcohol Use Disorders Identification Test (AUDIT) (also used for screening for eligibility) that has been found to be valid and reliable in identification of harmful and hazardous alcohol consumption [27]. The Big Five and the AUDIT inventories will be used in the baseline assessment only.

In addition, participants receiving vibroacoustic treatment will complete Visual Analogue Scale (VAS) before and after VAT to assess their condition at that particular moment. All the clients and therapists will also answer online questionnaires at the end of each session to evaluate the session and assess their emotional processing. The client questionnaire includes Emotional Processing Scale (EPS) and Session Evaluation Questionnaire (SEQ). The therapist questionnaire includes SEQ and additional open questions about each session. A subset of data about participants’ experiences will be collected through interviews to deepen the understanding and to interpret the results of the outcome measures. All the participants will evaluate their current mood on scale of 1–10 in the beginning of every therapy session.

#### Participant timeline {13}

There are overall four to five testing timepoints in this study: during the recruitment of the participants (baseline), 6 weeks after the beginning of the intervention (post-intervention), 6 months after the beginning of the intervention (first follow-up) and 12 months after the beginning of the intervention (second follow-up). The waiting-list control group will have an additional testing timepoint (baseline 2) at 6 weeks after the initial baseline tests before starting the therapy. This will also act as a new baseline for the intervention.

#### Sample size {14}

We will recruit 200 working-age adults (18–65 years of age) suffering from one or several of the following disorders: depression (ICD-10: F32 or F33), anxiety (ICD-10: F41), or exhaustion. The sample of participants will be randomised into four groups (50 + 50 + 50 + 50) of which two groups (*n* = 100) will receive vibroacoustic treatment (VAT) and two groups (*n* = 100) not whereas two groups (*n* = 100) will receive music listening (ML) and two groups (*n* = 100) not (see Table 2).

**Table 2 Tab2:** Factorial design

	VAT yes	VAT no	
ML yes	50	50	*n* = 100
ML no	50	50	*n* = 100
	*n* = 100	*n* = 100	

For each condition, the selected sample size provided a statistical power of 0.985 for detecting a medium standardised effect size of Cohen’s d = 0.5 in a mixed-model analysis [47], with a 2-tailed significance level of *p* < 0.05 and intra-participant correlation of ρ = 0.6. For the comparison between IIMT only vs waiting-list control, the selected sample size provided statistical power of 0.9 for detecting a medium effect size (d = 0.23) in a repeated measures t-test, with a 2-tailed significance level of *p* < 0.05. These high-power levels ensure a robust detection of clinically meaningful effects, even after accounting for potential participant dropouts, while reducing the likelihood of Type II errors. Also, the selected sample sizes also retain adequate power (> 0.8) to detect smaller effects (e.g., d = 0.2), thus providing sensitivity to subtle group differences.

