## Objectives {7}

The aim of the study is to focus on depression and anxiety symptoms of individuals of working age and to expand the scope to cover exhaustion as well. This RCT’s intervention is targeted at adult individuals who are in employment, in their studies, temporarily unemployed, on short-term sick leave or rehabilitation allowance and have one or various of the following disorders or conditions: depression, anxiety, work-related stress or exhaustion.

Objective 1: To examine whether IIMT, offered in four different modifications, improves the participants’ condition relative to the control/TAU (Treatment as usual) group. We also aim to find out whether any of the modifications of the IIMT are more effective than plain IIMT.

Objective 2: To understand whether certain musical responsiveness or personality profile explains a client’s improvement in music therapy.

Objective 3: To increase the understanding of the dynamics of therapeutic change by IIMT in its original form and with selected modifications.

Objective 4: To increase the understanding of the essence, mechanisms and trajectories of work-related stress and burnout and their relationship to depression and anxiety.

Hypothesis 1: All the experiment groups (ML + IIMT, VAT + IIMT, VAT + ML + IIMT) improve significantly relative to the control/TAU group.

Hypothesis 2: ML + IIMT group improves significantly better than the IIMT only group.

Hypothesis 3: VAT + IIMT group improves significantly better than the IIMT only group.

Hypothesis 4: VAT + ML + IIMT group improves significantly better than ML + IIMT, and VAT + IIMT groups.

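### The power of 0.985 given for each condition matches a factor-level comparison (100 v 100) and carries over to the 50 v 50 group contrasts of Hypotheses 2-4 only if VAT and ML do not interact

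*Protocol article*

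**What the plan says.** Sample size {14} fixes the group sizes: "The sample of participants will be randomised into four groups (50 + 50 + 50 + 50"). It then gives the factor margins, "two groups (*n* = 100) will receive vibroacoustic treatment (VAT) and two groups (*n* = 100) not", and the same for ML; Table 2 shows these margins. The power statement follows directly: "For each condition, the selected sample size provided a statistical power of 0.985 for detecting a medium standardised effect size of Cohen’s d = 0.5". The method named for it is a mixed model, "with a 2-tailed significance level of *p* < 0.05 and intra-participant correlation of ρ = 0.6". Neither a formula nor the number of visits entering the calculation is given, and no separate power is given for comparisons between two of the four groups in the mixed model.

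Trial design {8} uses the word condition for the four randomised groups, and the intervention sections label them Conditions A to D. Objectives {7} words the hypotheses by group. Hypothesis 2 sets ML + IIMT against IIMT only. The next two read: "Hypothesis 3: VAT + IIMT group improves significantly better than the IIMT only group" and "Hypothesis 4: VAT + ML + IIMT group improves significantly better than ML + IIMT, and VAT + IIMT groups".

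Statistical methods {20a} takes a different route. VAT and ML enter as factors, their effects are estimated through interactions with time, and the VAT × ML term is added only in an exploratory extension.

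**The concern.** Taken at its word, the sentence credits each group of 50 with 98.5% power. The inputs printed with it give that figure most directly for 100 v 100. In that comparison the control without ML pools IIMT only with VAT + IIMT, and the control without VAT pools IIMT only with ML + IIMT. The comparator named in Hypotheses 2 and 3 is the IIMT-only group alone.

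What is at stake is how a null result is read. If ML + IIMT is not shown to beat IIMT only, a reader who relies on 0.985 would put the chance of having missed a true d = 0.5 at 1.5%. For a direct comparison of the two groups that chance is larger on nearly every reasonable calculation, and the protocol offers no figure for it.

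**Working it through.** **Inputs.** From Sample size {14}: d = 0.5, two-sided alpha 0.05, ρ = 0.6, 50 per group, 100 per factor level. From Participant timeline {13}: three measurements after the start of therapy (6 weeks, 6 months, 12 months). Assumptions: all three visits enter the calculation, the correlation is the same between any two visits, and nobody drops out.

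**Formula.** With the single-visit SD set to 1, the mean of m visits has variance v = (1 + (m − 1)ρ)/m. For n per side, power = Φ(0.5/√(2v/n) − 1.96).

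**Reproducing the stated figure (100 v 100, m = 3).**
- v = (1 + 2 × 0.6)/3 = 0.733
- standard error = √(2 × 0.733/100) = 0.121
- 0.5/0.121 = 4.13
- power = Φ(4.13 − 1.96) = 0.985, the printed value. A noncentral t calculation gives 0.984.

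**Same calculation for two groups (50 v 50).**
- standard error = √(2 × 0.733/50) = 0.171
- 0.5/0.171 = 2.92
- power = Φ(2.92 − 1.96) = 0.83

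**How far this depends on the unstated formula.** Adjusting for baseline subtracts ρ² = 0.36 from v.

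| Analysis | v | 100 v 100 | 50 v 50 |
|---|---|---|---|
| Single visit, unadjusted | 1.000 | 0.942 | 0.705 |
| Mean of three visits, unadjusted | 0.733 | 0.985 | 0.831 |
| Single visit, baseline-adjusted | 0.640 | 0.993 | 0.878 |
| Mean of three visits, baseline-constrained | 0.373 | above 0.999 | 0.983 |

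The last row needs the full effect of 0.5 to persist to 12 months.

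**Hypothesis 4.** Suppose it is tested as two pairwise contrasts, D v B and D v C, both of which must succeed, with D better than each by 0.5. The contrasts share group D, so their correlation is 0.5. Joint power is 0.73 with v = 0.733, and 0.97 with v = 0.373.

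**Dropout.** No rate is stated. With v = 0.733, an assumed 10% loss (45 v 45) takes 0.83 to 0.79, and an assumed 20% loss (40 v 40) takes it to 0.74. The factor-level figure falls from 0.985 to 0.975 and 0.958.

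**Why the interaction decides the matter.** In the additive model the ML coefficient is estimated from the average of B − A and D − C, and the VAT coefficient from the average of C − A and D − B. Without an interaction, the two differences in each pair are equal. The ML coefficient is then the contrast of Hypothesis 2, the VAT coefficient is the contrast of Hypothesis 3, and all 200 participants inform each. With an interaction the differences in a pair diverge, the coefficient no longer equals the named group contrast, and that contrast must be estimated from two groups of 50.

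**The case against.** The best defence is that the plan schedules no 50 v 50 mixed-model test. Statistical methods {20a} estimates VAT and ML as factors, and in that additive model all the contrasts of Hypotheses 2-4 reduce to the two factor coefficients. For that analysis 0.985 is a fair figure. This stands, and it rules out calling the number a miscalculation.

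It can also be said that condition may loosely mean factor. The same section, in defining the overall treatment effect, refers to regression coefficients for each condition when the coefficients are those of VAT and ML. So usage is not uniform. But on that reading the sentence still needs the clearer word, and the group-worded hypotheses are left without a power figure unless additivity is assumed.

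Finally, the formula is not printed. The planned model constrains baseline, and the overall effect combines time points; that combination gives 0.983 at 50 v 50, close to the stated value. This cannot be excluded. It does not round to 0.985, however, whereas the unadjusted mean of three visits at 100 v 100 does, and it requires a sustained effect and complete data.

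A reader might infer that the sponsor's own calculation shows a flat loss of 15 points, or that a Hypothesis 2 or 3 test would miss a true d = 0.5 exactly 17% of the time. The protocol does not support this: 0.83 comes from a reconstructed formula and presumes a pairwise test that the analysis section does not specify.

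**Conclusion.** The power statement carries the wrong label. The figure of 0.985 matches VAT yes v no and ML yes v no at 100 v 100, and it is sound for those main effects given additivity and no dropout. Attached to each condition, and read alongside Hypotheses 2-4, it claims more than the protocol's figures support unless VAT and ML do not interact.

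For direct 50 v 50 comparisons at d = 0.5, power is about 0.83 by the calculation that reproduces the stated figure, within a range of 0.70 to 0.98 set by the visits used and the handling of baseline. For both parts of Hypothesis 4 as pairwise tests it is about 0.73, and up to 0.97 on the most favourable calculation. All of these assume no dropout. The attribution of 0.985 to 100 v 100 rests on an exact numerical match and on Table 2, not on a printed formula. None of this shows that the trial is too small.

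**What to change.** In Sample size {14}, replace the opening words of the power sentence with: For each factor (VAT yes v no, ML yes v no; 100 v 100, assuming no VAT × ML interaction and no dropout).

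Then add that direct comparisons between two groups of 50 have lower power at d = 0.5: about 0.83 by the calculation that reproduces 0.985, ranging from 0.70 (single visit, unadjusted) through 0.88 (single visit, baseline-adjusted) to 0.98 (baseline-constrained mean of three visits, effect sustained to 12 months). For Hypothesis 4, if both parts are tested as pairwise contrasts, add about 0.73 by the same calculation and up to 0.97 on the most favourable one. The sponsor holds the actual formula and should state it and print the single figure that follows from it in place of the range.

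The cost is a reworded paragraph and a less favourable stated power. Enrolment does not change.
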